### Usual care

Standard dietary and exercise advice will be emphasized before and after randomization for all women. At randomization and each clinical visit, a dietitian and a nurse will provide food intake education and information about GDM treatment.

### Aquatic exercise intervention

Participants commence the exercise session by performing stretching and an active warm-up of 5 minutes duration. Aquatic sessions include walking, walking backwards, swimming laps, jogging, step climbing and strength exercises in the water. After 35 minutes, the participants initiate a 5-minute cool down period.

Pool-based exercise classes will be completed in groups of four to six participants under the instruction of a physiotherapist. The exercise program will be conducted three times per week with each session lasting 45 minutes. This will be conducted from GDM diagnosis (26th to 28th gestational week) to the end of the third trimester (38th to 39th gestational week). Thus, an average of 30 training sessions will be planned for each pregnant woman.

The entire program will be developed in the thermal pool at IMIP; water temperature around 28°C.

All participants will use a heart rate monitor (Polar Electro OY) during the training sessions to ensure that heart rate is consistently under 70% of their age-predicted values.

A summary of the study design is presented in Figure 1.

**Figure 1 F1:**
[figure not shown]
Flow diagram of the aquatic physical exercise trial design.

### Analyses

Maternal and fetal characteristics of the study sample will be presented by group, intervention and control in terms of mean and SD. For group comparisons of glucose levels and perinatal variables, continuous and nominal data will be analyzed by t test for unpaired data and χ^2^ tests, respectively. Data will be analyzed using the intention-to-treat principle. Statistical analysis will be performed with STATA version 3.1 and the level of significance will set to <0.05.

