### Participant selection

Obstetrical staff will identify pregnant women recently diagnosed with GDM; following IMIP guidelines, a 75 g oral glucose tolerance test (OGTT) is routinely performed between the 24th and 28th gestational week. These patients will be approached by a member of the study team and permission will be sought after an explanation of the study goals. GDM women will be considered eligible for enrollment if they fulfill all the inclusion criteria and none of the exclusion criteria. Interested patients will be invited to sign a written informed consent.

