### Inclusion criteria

GDM diagnosis will be based on the IADPSG HAPO study (2 h, 75 g OGTT: fasting glucose ≥92 mg/dl or a 1-h result of ≥180 mg/dl, or a 2-h result of ≥153 mg/dl) [17]. Subjects must be aged 18 to 35 years and physically inactive (<150 minutes per week based on International Physical Activity Questionnaire) [18].

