### Sample size

The sample size was calculated with the aim of reducing glucose levels by 20% on average in the intervention group. A power of 80% and a level of significance of 5% was accepted, and thus the calculated sample size in each arm was 30 patients. Assuming a dropout of 20%, 72 pregnant women will be included in the study.

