### Randomization

Randomization will be performed according to a computed-generated allocation (http://www.randomized.com). Pregnant women will be assigned, in a 1:1 ratio, to exercise intervention or usual care. Blinding of the study to the randomization arm is not possible due to the nature of intervention.

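### Mean glucose is compared by an unadjusted t test although OGTT glucose is known before randomisation; the test is valid but gives up precision that one baseline covariate would probably recover

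*Protocol article*

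**What the plan says.** The test is fixed in the protocol article under Analyses: "For group comparisons of glucose levels and perinatal variables, continuous and nominal data will be analyzed by t test for unpaired data", with χ² tests for nominal data. The Abstract (Methods/Design) repeats it. No covariate, change score or repeated-measures model appears in either place. Under Post-randomization evaluations, the capillary profile is analysed after the intervention only, so no earlier glucose value enters the comparison.

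A baseline glucose measure exists by design. Participant selection says that "a 75 g oral glucose tolerance test (OGTT) is routinely performed between the 24th and 28th gestational week", and women are approached and asked for consent after that diagnosis. Inclusion criteria adds: "GDM diagnosis will be based on the IADPSG HAPO study", with thresholds for fasting, 1-h and 2-h glucose.

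On allocation, Randomization says: "Pregnant women will be assigned, in a 1:1 ratio, to exercise intervention or usual care". It mentions no stratification by baseline glucose.

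Sample size gives the target difference in these words: "The sample size was calculated with the aim of reducing glucose levels by 20% on average in the intervention group". The error rates are stated next: "A power of 80% and a level of significance of 5% was accepted". The result before any allowance for losses is that "the calculated sample size in each arm was 30 patients". The section then turns to losses: "Assuming a dropout of 20%, 72 pregnant women will be included in the study". No SD, control mean or baseline-outcome correlation is given.

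**The concern.** Glucose is both the entry measure and the primary outcome. The OGTT precedes randomisation, so treatment cannot affect it. Its fasting and 2-h values correspond to the fasting and 2-h postprandial capillary readings that make up the outcome. A t test that ignores it leaves in the error term all the outcome variance that the OGTT could explain.

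Two things are at stake in a trial of about 30 analysed women per arm. The first is precision: adjustment multiplies the residual variance by about 1 − r². The second is chance imbalance. With no stratification stated, the arms may differ in baseline glucose, and r times that difference remains in the unadjusted estimate. If adjustment is not specified in advance, an imbalance seen afterwards also invites a post hoc decision on whether to adjust.

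**Working it through.** **Inputs**

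- From Sample size: power 80%, significance level 5% (sidedness not stated; two-sided assumed), 30 per arm before dropout, 72 in total, dropout 20%, a 20% reduction in mean glucose.
- From Randomization: 1:1, so 72/2 = 36 per arm, and 36 × 0.8 = 28.8 evaluable per arm.
- Not in the document: the SD of mean glucose and the correlation r between OGTT glucose and the later capillary mean. The SD is back-solved; r is assumed over 0 to 0.5.

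**Step 1: the plan's own figure.** Thirty per arm cannot be derived without an SD, so I solved for the standardised effect d that gives 80% power. By the normal approximation, d = (1.960 + 0.842) × √(2/30) = 0.723, which implies a coefficient of variation of 0.20/0.723 = 27.6%. By the noncentral t distribution, d = 0.736 and the coefficient of variation is 0.20/0.736 = 27.2%. I use 0.736.

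**Step 2: unadjusted power.** With n = 28.8 per arm, the noncentrality is d × √(n/2) = 0.736 × √14.4 = 2.79 on 2n − 2 = 55.6 degrees of freedom. Power is 78.3%.

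**Step 3: ANCOVA with one covariate.** The residual SD shrinks by √(1 − r²). One degree of freedom is lost (54.6 remain). Estimating the slope inflates the variance by about 1 + 1/(2n − 4) = 1 + 1/53.6 = 1.019. The noncentrality is therefore 2.79 / √[(1 − r²) × 1.019].

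| Assumed r | 1 − r² | Noncentrality | Power |
|---|---|---|---|
| t test, no covariate | – | 2.79 | 78.3% |
| 0 | 1.00 | 2.77 | 77.5% |
| 0.2 | 0.96 | 2.82 | 79.2% |
| 0.3 | 0.91 | 2.90 | 81.3% |
| 0.4 | 0.84 | 3.02 | 84.2% |
| 0.5 | 0.75 | 3.19 | 88.0% |

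Adjustment gains power once r exceeds about 0.14, and brings power back to 80% once r exceeds about 0.24. If a second covariate is added, the two thresholds rise to about 0.19 and 0.28, with r read as the multiple correlation.

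**Step 4: chance imbalance.** At 30 per arm, one standard error of the baseline difference is √(2/30) = 0.26 SD. Unadjusted, it moves the glucose difference by r × 0.26 SD:

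- r = 0.3: 0.08 SD, about 11% of d.
- r = 0.5: 0.13 SD, about 18% of d.

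Given an imbalance of 1.96 standard errors, the conditional two-sided type I error of the t test is 7.9% at r = 0.3 and 12.9% at r = 0.5. Given an imbalance of one standard error, it stays near 5% (5.0% and 4.8%). Averaged over all randomisations it is 5%.

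**The case against.** The strongest reply is that nothing here is invalid. Under randomisation the unpaired t test is unbiased and holds its type I error, which already allows for chance imbalance. That stands. A reader might infer from the conditional figures that the planned test is biased; the document does not support this, because those figures describe one unlucky allocation and not the long-run behaviour of the test. Nor does an imbalance pass into the estimate in full: only r times it does.

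A reader might also infer that adjustment is free, or that it is sure to make up for the dropout allowance, which leaves 28.8 per arm when 30 were planned. Neither follows. At r = 0 the adjusted analysis loses about 0.8 points (78.3% to 77.5%), and 80% is reached only above r of about 0.24.

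There are reasons to expect a modest r. The OGTT is a glucose challenge at weeks 24 to 28, whereas the outcome is a mean of capillary readings taken after the intervention, on dietary advice. The entry thresholds narrow the OGTT range. Insulin is introduced in response to high readings (Post-randomization evaluations), which may weaken the link between baseline and outcome. All of this limits the size of the gain, not its direction once r exceeds about 0.14.

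Availability has a limit too. The diagnostic thresholds are alternatives, and some women are referred from elsewhere (Setting and recruitment), so a complete set of OGTT values for every woman is likely but not stated.

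Finally, a statistical analysis plan that is not shown may add adjustment. That would be welcome, but it would depart from the method the article states. The point concerns that stated method, not an omitted detail.

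**Conclusion.** The point holds as one of efficiency, not validity. The article specifies an unadjusted test for a continuous primary outcome although a closely related baseline measure exists before randomisation. For assumed r between 0.2 and 0.5, adjustment adds about 1 to 10 power points (78.3% to between 79.2% and 88.0%) and removes chance OGTT imbalance from the estimate, apart from error in the estimated slope. If the OGTT does not predict the outcome, the loss is under one point.

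These figures rest on a two-sided test, d = 0.736 back-solved from 30 per arm, 28.8 evaluable women per arm, and an assumed r. None of them shows what this trial's power will actually be, since the SD is not stated. The point covers the mean fasting and postprandial glucose comparisons only; it does not extend to insulin use or the other χ² endpoints. It is worth changing before analysis, but the trial would not be invalid without it.

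**What to change.** In Analyses, and correspondingly in the Abstract, replace the t test for the continuous glucose means with an ANCOVA containing arm and one pre-specified baseline covariate: OGTT fasting glucose for the fasting mean, OGTT 2-h glucose for the postprandial mean. Report the adjusted difference with its 95% confidence interval, and keep the unpaired t test as a sensitivity analysis. One covariate per model is enough. The document states no link between gestational age at entry and the outcome, and adding it raises the r needed to break even from about 0.14 to about 0.19.

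Before the data are compared by arm, confirm that both OGTT values are on file for referred women, and state how a missing baseline value will be handled.

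The cost is one or two sentences in the plan. No new visits, measurements or participants are needed.

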### Ethics

This study was approved by the IMIP Research Ethics Committee. All participants must sign an informed consent before admission to the study. A steering committee was established to monitor the trial.

## Discussion

Currently, there is a lack of evidence regarding the association between physical exercise and GDM control. To the best of our knowledge, this is the first randomized controlled trial evaluating the effects of an aquatic physical exercise program on GDM outcomes. Water provides resistance to muscle movement, resulting in higher workout intensities without gravitational stress and pain as well as a massaging effect. These effects may facilitate the practice of physical exercise by pregnant women and thus increase compliance.

During pregnancy, women decrease their physical activity level, especially in the last trimester. Physical exercise in water is more feasible and may be more suitable for pregnant women. Additionally, doing exercise in groups can contribute to socialization and help ensure greater adherence.

Although our study will be performed in tropical weather, temperature approximately 28°C to 30°C year round, by using a thermal pool our results can be extrapolated to other regions with colder temperatures.

This project has several methodological strengths. First, it is safe for pregnant women. Aquatic physical exercise will be supervised by a physiotherapist, all participants will wear a heart rate monitor and the intensity of the physical exercise will be low to moderate. Only women who live in the metropolitan region will be included and all transportation cost will be covered. Bathing suits and lunch will also be supplied to the participants. We believe that these measures will ensure greater adherence to the study.

Our study has some methodological weaknesses that will be taken into account, but that are unlikely to influence ours findings. Our close monitoring of physical activity among all participants via the wearing of a pedometer may allow us to verify if the two groups are maintaining the same physical activity level outside of the aquatic physical exercise.

In conclusion, this study is expected to provide findings that may reveal the true effect of aquatic physical exercise on GDM control.

## Trial status

This trial is registered under: NCT01940003. Recruitment commenced in August 2013 and is expected to continue until March 2014. Open for recruitment.

## Abbreviations

GDM: gestational diabetes mellitus; HAPO: Hyperglycemia and adverse pregnancy outcomes; IADPSG: International association of the diabetes in pregnancy study group; IMIP: Instituto de Medicina Integral [name].
